### Ethics

This study obtained ethics approval from the University of Melbourne (1543797.1) and University of Ibadan/University College Hospital Ethics Committee, Ibadan, Nigeria (UI/EC/16/0413). We registered the trial on the Australian and New Zealand Clinical Trials Registry (ACTRN12617000341325). Data monitoring will be done by the lead author, reporting to an advisory committee every 6 months.

## Discussion

This project is part of a multi-country implementation research project based in Nigeria and Papua New Guinea [47], which seeks to test and build upon the implementation lessons learnt from oxygen projects in Papua New Guinea [9, 14] and elsewhere [10]. By using a realist approach to project design and evaluation, this project will provide information not only on *what* works, but *how* it works in different contexts. We consider this information critical to meaningfully scale up oxygen therapy globally and ensure that this basic medical therapy is available to those who need it the most.

Two previous oxygen projects have demonstrated that improved oxygen systems can improve paediatric pneumonia outcomes for hospitalised children [9, 15]. This project will advance the evidence on effectiveness using a rigorous, randomised control design to evaluate clinical outcomes in admitted children and neonates in a challenging sub-Saharan African setting.

At the time of writing we have commenced activities in all 12 participating hospitals. We completed a needs assessment and participatory planning process in 2015, and implemented the full oxygen system in the first three hospitals in April 2016. The final three hospitals have commenced intervention activities in March 2017, as scheduled. The main implementation challenges encountered so far have related to the development and testing of the solar power systems, necessitating a complete redesign and pilot testing of the system. We took alternative measures in the interim to improve and stabilise the power systems for the early intervention hospitals and were able to complete full implementation of the improved oxygen systems according to the planned stepped-wedge timeline.

As expected, different hospitals have taken slightly different approaches to particular aspects of the intervention. For example, while hospital administrators have been open to alternative financing structures for oxygen, the actual implementation of this has been difficult in some hospitals due to administrative and governance requirements. We have been impressed with the ingenuity and problem-solving capacity of the participating hospitals, but informal feedback shows significant variability in the functioning of teams at different hospitals. This highlights the importance of measuring and reporting fidelity and other process indicators, in order to better understand this variability and how improved oxygen systems work in different contexts. Overall, the intervention appears to be achieving very high levels of fidelity, and early data shows large improvements in oxygen-related clinical behaviours (e.g. the use of pulse oximetry, administration of oxygen to hypoxaemic patients, etc.). Interim safety data suggests that the intervention is not causing harm and probably causing benefit, and we anticipate having adequate power to detect a meaningful difference by the end of data collection despite lower than expected admission numbers.

Oxygen therapy is a basic, life-saving therapy that is relevant for many paediatric and adult health conditions, but has limited global availability. Our study should provide quality evidence on the effectiveness of improved oxygen systems, and how to better implement and scale up oxygen systems in resource-limited settings. Our results will have important implications for policy-makers, hospital administrators, and child health organisations in Africa and globally. Our findings may have broader applicability to other healthcare interventions that are worthy of scale-up but are proving challenging to implement in the places that can benefit the most.

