We made a pragmatic decision to define clusters at the hospital level, as this was the natural level at which the intervention would be implemented and geographic separation between hospitals meant there was minimal risk of contamination. We considered clustering at the sub-hospital level (e.g. by ward), but rejected this due to the heterogeneity of ward arrangements, the large cross-over between wards, and the logistical complications that would have resulted. We randomised groups of three hospitals to receive the intervention at four different time-points (steps), spaced 4 months apart. This was based on practical considerations (i.e. how many hospitals could be practically set-up at a particular point in time), effect considerations (i.e. the effect should be realised within this time period), and statistical considerations (i.e. balancing the number of steps with the number of clusters within each step). We considered pairing clusters (hospitals), but rejected this due to the low number of included hospitals. We nominated a 3-week cross-over time for each hospital as it ‘stepped’ into the intervention, as this would be adequate time for the intervention to be fully implemented and pre-intervention patients to be discharged (to avoid contamination). We determined that data collection would be cross-sectional, measured at multiple points before and after the intervention at the level of individual patients (and anticipating a low rate of re-admission during the trial period).

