### Study setting

This study is based in 12 secondary-level hospitals across four states (Oyo, Ondo, Ogun, and Osun) in southwest Nigeria (Table 2). In a three-tier health system, secondary-level hospitals have an important role in providing first-contact hospital care for the population. We wanted to conduct this study in hospitals that would be representative of secondary-level hospitals treating children in a challenging, high-mortality environment, to ensure that findings would be most relevant for future scale-up in Nigeria and sub-Saharan Africa more broadly.

**Table 2 Tab2:** Characteristics of 12 secondary-level hospitals in southwest Nigeria: paediatric and neonatal wards (adapted from baseline needs assessment [8])

	1	2	3	4	5	6	7	8	9	10	11	12
Hospital type	State	Mission	Mission	State	State	State	State	State	Mission	Mission	Mission	State
Beds (child + neonatal)	13 (9 + 4)	32 (20 + 12)	63 (38 + 25)	36 (26 + 10)	46 (22 + 24)	60 (44 + 16)	48 (20 + 28)	36 (16 + 20)	20 (15 + 5)	14 (12 + 2)	70 (40 + 30)	25 (21 + 4)
Admissions (annual)	185	507	2343	238	791	849	3431	1945	431	344	2345	744
Child	180	444	1649	231	552	679	1959	1111	292	325	972	683
Neonate	5	63	693	7	239	170	1473	834	139	19	1373	61
Staffing												
Access to paediatrician	No^a^	No^a^	Yes^b^	No^a^	No	Yes	Yes	Yes	Yes	Yes^b^	Yes^b^	Yes
Medical (entire hospital)	7	4	6	7	12	17	16	11	5	6	4	2
Nursing (paediatric)	11	7	18	26	31	62	26	33 (3)	9 (2)	4	18	16 (2)
Power supply (h/day) power interruptions	6–12 hourly	6–12 hourly	12–18 hourly	6–12 hourly	6–12 hourly	12–18 hourly	12–18 hourly	6–12 hourly	>18 > daily	>18 > daily	12–18 hourly	6–12 hourly
Oxygen supply	Poor	Poor	Poor	Poor	Fair	Poor	Poor	Poor	Fair	Poor	Poor	Poor
Oxygen cylinders	Yes^d^	Yes^d^	Yes	Yes^d^	Yes	Yes	Yes^c^	Yes	Yes^d^	Yes^d^	Yes^d^	Yes^d^
Oxygen concentrators	No	No	Yes^e^	No	No	No	Yes^e^	Yes^e^	Yes	Yes^e^	Yes^e^	Yes^e^
Pulse oximeters	No	No	No	No	No	Yes	No	No	Yes	Yes	No	No
Maintenance capacity and procedures	Poor	Poor	Poor	Poor	Poor	Poor	Poor	Poor	Poor	Poor	Fair	Fair
Clinical guidelines, education and review	Poor	Fair	Poor	Poor	Fair	Poor	Good	Fair	Fair	Poor	Fair	Poor
Care systems												
Clinical records	Fair	Fair	Fair	Fair	Fair	Fair	Fair	Fair	Fair	Fair	Fair	Fair
Administrative records	Poor	Poor	Poor	Poor	Poor	Poor	Poor	Poor	Poor	Fair	Fair	Poor
Medication and supplies	Good	Good	Good	Good	Good	Good	Good	Good	Good	Good	Good	Good
Infection control	Good	Good	Good	Good	Good	Good	Good	Good	Good	Good	Good	Good

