Strengthening quality improvement processes continuing education and morbidity review demonstrating quality improvement process quality improvement team building	To strengthen broader care processes To strengthen managerial support for oxygen therapy To build and sustain healthcare worker capacity and motivation to provide good clinical care To stimulate healthcare workers to make their work environment more conducive to good clinical care To build hospital team capacity to maintain and scale up oxygen systems	Support ongoing education and clinical review activities, including retraining as staff rotate Demonstrate behavioural and structural changes regarding oxygen therapy. Encourage development, and support function, of multidisciplinary teams at the hospital level Embedded project nurse within each hospital to collect data, and support project activities

Equipment manufacturers: Airsep, Buffalo, OH, USA (subsidiary of Chart Inc.); Lifebox Foundation, London, United Kingdom (http://www.lifebox.org/). We recommended the use of Airsep Newlife Elite concentrators and Lifebox pulse oximeters based on results of previous technical assessments [49–51], affordability, and field experience in resource-limited settings [10, 52]

During phase II, the coordination team will visit at least every 3 months, to provide supportive supervision, feedback, and collect user feedback. In keeping with the ideals of quality improvement, we will review ongoing user feedback and interim data to monitor implementation and enable timely response to problems in the field. Feedback to the hospitals may include written reports to congratulate them for their progress, and to inform them of how other sites are going and what the next steps in implementation may be.

Hospitals will step into phase II at different times according to pre-defined random allocation. As such, hospitals will be in phase I for between 4 and 16 months, and in phase II for between 8 and 20 months, with a total period of 24 months of prospective data collection.

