### Sample size

We made sample size and power estimates using the Stata menu-driven programme *steppedwedge*, which is based on the Hussey and Hughes’ method for calculating sample size for a stepped-wedge trial [44, 45]. We based our assumptions on admission, prevalence, and case-fatality rate data from our needs-analysis, and informed by correlation estimates from previous studies [46]. We estimated that we would enrol approximately 16,770 children and 7670 neonates (1290 preterm) over the course of the study. Based on an alpha of 5%, we calculated that we would have approximately 80% power to detect a 35% reduction in pneumonia case fatality rate (6.1% to 4%), and 90% power to detect a 20% reduction in neonatal case fatality rate (8.2% to 6.6%). We would have greater than 90% power to detect 10% change in quality of care scores.

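### The Discussion expects adequate power despite low admissions but gives no recomputed figure, and the 90% neonatal power does not follow even from the planned 7,670 neonates

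*Protocol article*

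**What the plan says.** Protocol article, Sample size: "We estimated that we would enrol approximately 16,770 children and 7670 neonates (1290 preterm) over the course of the study". At a 5% alpha, the section then gives approximately 80% power for a 35% reduction in pneumonia case fatality (6.1% to 4%) and 90% power for a 20% reduction in neonatal case fatality (8.2% to 6.6%). The method named is Hussey and Hughes, run through a Stata stepped-wedge program. On inputs it says: "We based our assumptions on admission, prevalence, and case-fatality rate data from our needs-analysis". It adds that correlation estimates came from previous studies, but prints no value.

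Table 1 (Study design) fixes 12 hospitals in four groups of three and six 4-month periods. The Intervention section closes the window, "with a total period of 24 months of prospective data collection".

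The Discussion, written while the trial was running, says: "we anticipate having adequate power to detect a meaningful difference by the end of data collection despite lower than expected admission numbers".

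**The concern.** The printed power is conditional on an enrolment figure, and the article reports that admissions are below expectation. With hospitals, periods and duration fixed, fewer admissions mean smaller hospital-period cells and less information. Pneumonia power was only about 80% at full planned enrolment, so it had no reserve. The Discussion nevertheless offers reassurance and leaves the Sample size figures as the only numbers a reader can attach to it.

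This matters most if the mortality result is null. Readers would take it as coming from a trial with 80-90% power for reductions of 35% and 20%, and would treat it as evidence against effects of that size. For neonates that reading would be wrong even if every planned admission had accrued.

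**Working it through.** **Inputs.** Planned enrolment, event rates, alpha and method are from Sample size. I = 12 hospitals and T = 6 periods are from Table 1. Three hospitals cross at each of steps 2, 3, 4 and 5 (Allocation). Three inputs are assumptions because the article does not give them: a two-sided test, equal cell sizes, and an intra-cluster correlation (ICC) between 0 and 0.2.

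**Formula (Hussey-Hughes).**
Var = I·s²·(s² + T·t²) / [(I·U − W)·s² + (U² + I·T·U − T·W − I·V)·t²]
Here s² is the variance of a cell mean, p(1−p)/n, with p the average of the two rates; t² = ICC/(1−ICC) × p(1−p); and power = Φ(difference/√Var − 1.96).

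Design constants:
- U = 3 × (5+4+3+2) = 42
- W = 0² + 3² + 6² + 9² + 12² + 12² = 414
- V = 3 × (25+16+9+4) = 162
- I·U − W = 90
- U² + I·T·U − T·W − I·V = 1764 + 3024 − 2484 − 1944 = 360

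**Step 1: neonates at planned enrolment (stated power 90%).**
n per cell = 7,670/72 = 106.5. p = 0.074, p(1−p) = 0.0685, s² = 0.000643. The difference is 0.016.
- ICC 0: Var = (12/90) × 0.000643 = 0.0000858; SE = 0.00926; z = 1.73; power = Φ(1.73 − 1.96) = 41%.
- ICC 0.2: Var = 0.000128; SE = 0.0113; z = 1.41; power = Φ(1.41 − 1.96) = 29%.

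The stated 90% is not reproduced. It would need about 27,000 neonates at ICC 0 and about 40,500 at ICC 0.2.

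**Step 2: do other readings recover 90%?**

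| Variant at 7,670 neonates | Power |
|---|---|
| One-sided 5%, ICC 0 to 0.2 | 41-53% |
| Five periods instead of six, ICC 0 to 0.2 | 31-47% |
| Exact 20% reduction (6.56%), ICC 0.001 to 0.1 | 31-38% |
| Hospital sizes in proportion to Table 2, ICC 0.001 to 0.1 | 27-36% |
| Individual 1:1 randomisation, no clustering, two-sided | 76% |
| The same, one-sided | 85% |

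None does. A value near 91% appears if all 7,670 neonates are counted afresh in each of five periods (ICC 0.01 to 0.1). That is only a possible explanation; the article does not say this was done.

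**Step 3: neonates at an assumed 20% shortfall.**
0.8 × 7,670 = 6,136, or 85.2 per cell. z falls to 1.55 (ICC 0) and 1.26 (ICC 0.2), giving power of 34% and 24%.

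**Step 4: pneumonia.**
The 80% cannot be reproduced, because the expected number of pneumonia cases is not printed. By the same formula it needs about 8,200 cases (ICC 0) to 12,270 (ICC 0.2), which is 49-73% of 16,770 child admissions. Taking 80% at face value, and letting information scale with the fraction f of expected pneumonia cases that accrue, power = Φ(2.80·√f − 1.96):
- f = 0.9: Φ(0.70) = 76%
- f = 0.8: Φ(0.55) = 71%
- f = 0.7: Φ(0.38) = 65%

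**The case against.** The Discussion sentence is a hedged forecast. It discloses the shortfall, does not repeat 80% or 90%, and refers to an undefined meaningful difference. It also leaves the baseline for expected admissions undefined, although the Sample size figures are the natural reading. No admission count is given, and the article does not say whether pneumonia, other child or neonatal admissions fell. Higher mortality or a larger effect could offset a shortfall, though the article cites neither as its reason. All of this stands, and it is why the pneumonia losses above are illustrations and not estimates. It does not supply support for the claim. The neonatal result in Step 1 needs no accrual figure at all.

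A reader might also infer that planned enrolment is itself an arithmetic error. Table 2 sums to 9,077 child and 5,076 neonatal admissions a year, or 18,154 and 10,152 over 24 months. The planned figures are 92% and 76% of those, and removing the 3-week cross-over windows leaves about 17,630 and 9,860. The documents do not support calling this an error. The article says only that its assumptions were based on needs-assessment data, and different discounts for children and neonates are possible, particularly as Table 2 rates administrative records poor at 10 of 12 hospitals. A condensed article need not print those discounts, and the gap runs in the cautious direction. Using the larger total would not rescue the neonatal claim either: 10,152 neonates give 37-51% power over the same ICC range.

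A second tempting reading is that neonatal power slips from 90% to somewhat less, such as 83% at a 20% shortfall. That calculation starts from a 90% the named method does not produce.

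**Conclusion.** The point holds in two parts.

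- **Pneumonia.** The assertion of adequate power is unsupported by any figure, and on the plan's own assumptions any shortfall in pneumonia cases puts power below 80%. The size of the loss is unknown. The 76%, 71% and 65% rest on assumed shortfalls of 10%, 20% and 30%, on pneumonia cases falling in proportion, and on accepting the stated 80%.
- **Neonates.** The stated 90% does not follow from 7,670 under the named method. Power is about 29-41% at full enrolment and about 24-34% at an assumed 20% shortfall, given a two-sided 5% test, equal cells and an ICC of 0 to 0.2. This is the larger problem.

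The documents do not show that pneumonia power has fallen to any particular level, or that the 80% was miscalculated, because neither the expected nor the accrued number of pneumonia cases is printed.

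**What to change.** 1. In the Discussion, replace the assertion with power, or the detectable relative reduction, recomputed by the stated stepped-wedge method at the admissions actually accruing per hospital and 4-month step. Report pneumonia cases and neonates separately, state the ICC, and use no interim effect estimates.
2. In Sample size, print the ICC, the sidedness and the expected number of pneumonia cases, and restate the power where it does not reproduce, in particular the 90% for neonates.
3. Do not raise expected enrolment to the Table 2 totals; that would move the planning figure up while admissions are reported as running low.

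The cost is a short recalculation from admission counts already being collected, and a few sentences of text. The downside is a less favourable stated power. No added enrolment or longer follow-up is proposed.

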### Trial status

This trial is underway. Recruitment, clinical data collection, project team visits, and interviews are all ongoing.

## Abbreviations

BCW: Behaviour Change Wheel
GEE: Generalised estimating equations
GLMM: Generalised linear mixed model
PAQC: Paediatric Admission Quality of Care
SpO_2_: Blood oxygen saturation measured by pulse oximetry
TDF: Theoretical Domains Framework
U/5: Under 5 years of age
WHO: World Health Organisation
